### Interventions

2.5

All participants will receive conventional treatment, including nonoperative managements, initially, and perhaps further surgical intervention if indicated according to the Bologna guidelines of ASBO^[3]^ and the trauma gastrointestinal surgeons’ expertise. Therapeutic efficacy will be defined by the appearance of flatus/defecation, radiological improvement, relief of abdominal symptoms, decreased drainage volume of nasogastric decompression, disappearance of air-fluid levels, or reduced gas and fluid in bowel loops. The nasogastric tube will be removed when the drainage output decreases to less than 200 ml per day or flatus/defecation occurs. A liquid diet will be administered gradually, typically followed by a soft diet and then solid food as tolerated. Patients will be discharged when solid food is well tolerated. If the patient presents no improvement and progresses into strangulation, peritonitis, or bowel ischemia, surgery will be recommended.^[3]^

The participants in each group will undergo real LA or sham LA treatment once daily for 6 days, using a gallium aluminum arsenide Laser Pen (maximal power, 150 mW; wavelength, 810 nm; area of probe, 0.03 cm^2^; power density, 5 W/cm^2^; pulsed wave; and Bahr frequencies (B1: 599.5 Hz, B2: 1199 Hz, B3: 2398 Hz, B4: 4776 Hz, B5: 9552 Hz, B6: 19,104 Hz, and B7: 38,208 Hz]; RJ-Laser, Reimers & Janssen GmbH, Waldkirch, Germany). We will use the same acupoints and manipulations in both groups. The participants in the control group will receive SLA treatment without any laser output (no stimulation), while the participants in the experimental group will sequentially receive 0.375 J of energy at each of the following acupoints: LI4 (Hegu, B3), PC6 (Neiguan, B3), ST25 (Tianshu, B3), ST36 (Zusanli, B2), CV4 (Guanyuan), and CV12 (Zhongwan, B3) (Fig. 2). The laser treatment will be applied to each point for 5 seconds to deliver a total treatment dose of 4.5 J/cm^2^. All acupoints have been selected and localized according to the WHO Standardized Acupuncture Point Location guidelines.^[8]^ In all the subjects, the laser application will be performed by the same experienced physician, who has sufficient training and is a licensed Chinese medicine practitioner in Taiwan.

**Figure 2 F2:**
[figure not shown]
Acupoints used in the study: LI4, PC6, ST25, ST36, CV12, and CV4.

### Outcome measurements

2.6

The primary outcome measurement will be the success of conservative treatment, which is defined as no need for nasogastric tube decompression or operative intervention. Secondary outcome measurements will include time to oral intake, length of hospital stay, and changes in serum amylase, lipase, cortisol, motilin, ghrelin, and I-FABP levels, which will be checked before the intervention, on the fourth day, and on the day of discharge, respectively. The reasons why participants are unable to complete the follow-up treatments or withdraw from the study, such as adverse events, suboptimal response to therapy, surgical intervention for ASBO, or refusal to receive intervention, will be recorded.

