## Abstract

**Background::**

Adhesive small bowel obstruction (ASBO) is one of the most common complications and is a major cause of re-admission after intra-abdominal surgery. The initial management of patients with ASBO is nonoperative treatment such as nil per os and decompression using a nasogastric tube. However, the ideal management of ASBO remains controversial.

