### Sample size, blinding, and randomization

2.4

As no related studies on the effects of acupuncture or laser acupuncture for the treatment of ASBO have been published, we determined the necessary sample size based on a previous study of the effects of sesame oil on ASBO.^[7]^ The surgical rate was 12.9% in the experimental group and 48.5% in the control group. Anticipating a power of 95% (1-β = 0.95), statistical significance (α = 0.05) of 95%, and a dropout rate of 10%, a total of 92 participants will be required in this study, according to G∗power analysis.

All the participants will be informed that they will receive laser acupuncture in addition to the conventional treatment and assess the efficacy of laser acupuncture for ASBO. The laser acupuncture devices used in the LA and SLA groups will have the same appearance. The difference will be that no energy will be output during the intervention in the SLA group. The participants will be unable to recognize whether they are being treated or not because laser acupuncture involves low-intensity, non-thermal laser irradiation that it is hard to detect. Participants will be randomly allocated to either the LA or the SLA group in a 1:1 ratio using computer-generated random numbers. Randomization will be performed by an independent researcher with no involvement in the inclusion and exclusion process, treatment, or outcome assessments.

The participants, outcome assessors, and data analysts will be blinded to the allocation of interventions using labels A and B for the 2 groups until the trial is completed.

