## Discussion

3

Typically, non-invasive methods applied to confirm of ASBO include a history of previous episodes of bowel obstruction by adhesions, or exclusion of other causes of bowel obstruction by imaging.^[3]^ The initial nonoperative management of patients with ASBO during first 72 hours, such as nil per os and decompression using a nasogastric tube or long intestinal tube, is safe and appropriate unless there are signs of peritonitis, strangulation, bowel ischemia, or other signs of clinical deterioration.^[3,4]^ Previous research found that the average length of stay in hospitals for ASBO was 7.8 days, and the in-hospital mortality from ASBO was 2.5%.^[1]^ Overall, recurrence or readmission due to ASBO is common, occurring in about 20% of patients.^[9,10]^ Although the risk of recurrence is slightly lower after operative treatment,^[9]^ this may not be the reason for deciding whether or not to prescribe a surgical intervention. Currently, the use of surgery to treat ASBO is controversial because such a procedure may induce the formation of new adhesions, increase postoperative morbidity, and length of hospital stay, incur higher associated costs as compared with nonoperative treatment, and significantly reduce postoperative quality of life.^[3,10,11]^Therefore, it is of great significance to find a treatment that can improve the success rate of conservative treatment for ASBO.

Acupuncture therapy, one of the most popular forms of complementary and alternative medicine (CAM), is used for the treatment of a variety of conditions.^[12]^ LA is a type of photo biomodulation under the instruction of traditional Chinese medicine theory. It involves stimulation of traditional acupoints with low-intensity, non-thermal, noninvasive laser irradiation.^[13]^ LA has become more common among acupuncture practitioners in recent years for its minimal sensation, short duration of treatment, and minimal risks of infection, trauma, and bleeding complications.^[13]^ LA has been shown to inhibit formations of postoperative intra-abdominal adhesions in animal studies.^[14,15]^ However, as far as we know, no trials have examined the clinical efficacy of acupuncture or LA on ASBO. Thus, we designed this trial to investigate the benefits and adverse events of LA in patients with ASBO.

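### The primary outcome counts need for nasogastric decompression as failure of conservative treatment, although the protocol makes decompression part of that treatment and sizes the trial on surgery alone

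*Protocol article*

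**What the plan says.** Four parts of the protocol article bear on this.

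- **Outcome measurements (2.6)** names the primary outcome as "the success of conservative treatment, which is defined as no need for nasogastric tube decompression or operative intervention". It gives no time point and no rule for a tube already in place.
- **Abstract (Background) and Discussion** describe the conservative treatment itself. The abstract states: "The initial management of patients with ASBO is nonoperative treatment such as nil per os and decompression using a nasogastric tube". The Discussion says that nonoperative management in the first 72 hours, "such as nil per os and decompression using a nasogastric tube or long intestinal tube, is safe and appropriate", subject to the usual danger signs.
- **Interventions (2.5)** says "All participants will receive conventional treatment, including nonoperative managements, initially". It then presupposes tubes in use during the trial: "The nasogastric tube will be removed when the drainage output decreases to less than 200 ml per day or flatus/defecation occurs". Among the signs of benefit it lists "decreased drainage volume of nasogastric decompression".
- **Sample size, blinding, and randomization (2.4)** bases the calculation on an earlier study of sesame oil: "The surgical rate was 12.9% in the experimental group and 48.5% in the control group". With 95% power, α = 0.05 and 10% dropout it arrives at 92 participants.

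**The concern.** The outcome is meant to show whether conservative treatment worked, yet one of its two failure components is the use of that treatment. Take a patient who is decompressed by tube, drains less each day, has the tube removed under the protocol's own rule and is discharged without an operation. By the abstract, Interventions and Discussion this is a conservative success. By the wording of Outcome measurements it is a failure.

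Timing makes this worse. The Participants section has the surgical team managing patients from admission, whereas Study design starts laser or sham only after enrolment. A tube placed in between cannot depend on allocation. Failures of that kind add equally to both arms and dilute the contrast.

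The sample size calculation uses surgery and nothing else. The article gives no rate for the composite of tube need or surgery, so the power claim has not been made for the outcome that will be tested. If the wording stays open, the reading could also be chosen once results are known.

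**Working it through.** **Step 1. Reproduce the planned size.** Inputs from section 2.4: p1 = 0.129, p2 = 0.485, α = 0.05 (taken as two-sided), power 0.95, dropout 10%, allocation 1:1. Pooled-variance formula without continuity correction, with p̄ = (0.129 + 0.485)/2 = 0.307:

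n per arm = [1.960·√(2p̄(1−p̄)) + 1.645·√(p1(1−p1) + p2(1−p2))]² / (p2 − p1)²
= [1.960·√0.4255 + 1.645·√0.3621]² / 0.356² = 40.6, so 41.

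Total 82; 82/0.90 = 91.1, so 92. The stated figure is reproduced exactly, for surgery as the event.

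**Step 2. Compare the two events.**

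| | Sizing (2.4) | Primary outcome (2.6) |
|---|---|---|
| Failure | Surgery | Tube need or surgery |
| Rates given | 12.9% vs 48.5% | None |
| Time point | None | None |

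**Step 3. Illustrate the literal reading.** Let g be the share of patients already counted as failed at baseline because of a tube. The documents do not give g. Assume that it is equal in both arms and independent of surgical risk, and that no further failures arise from tube need after randomisation. Then

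failure rate = g + (1 − g) × surgical rate,

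and the difference between arms shrinks to (1 − g) × 35.6 percentage points. Example, g = 0.30: 0.30 + 0.70 × 0.129 = 0.390 and 0.30 + 0.70 × 0.485 = 0.640.

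Power is from exact binomial enumeration of the two-sided uncorrected chi-squared test with 41 per arm:

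| g | Failure, laser | Failure, sham | Power |
|---|---|---|---|
| 0 | 12.9% | 48.5% | 95% |
| 10% | 21.6% | 53.7% | 87% |
| 30% | 39.0% | 64.0% | 66% |
| 50% | 56.5% | 74.3% | 40% |
| 80% | 82.6% | 89.7% | 16% |

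The normal approximation is close (39% at g = 50%, 15% at g = 80%). At g = 100% nobody can succeed and the comparison carries no information.

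**Step 4. Check the alternative endpoint.** With surgery as the primary event, Step 1 applies and 92 stands, provided the sizing rates hold. The Introduction reports that 70% to 90% of patients respond to nonoperative treatment. If the rest have surgery, that suggests a surgical rate of about 10% to 30%, not 48.5%. Keeping the planned relative risk, 0.129/0.485 = 0.266, exact power with 41 per arm is:

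| Control rate | Laser rate | Power |
|---|---|---|
| 10% | 2.7% | 29% |
| 20% | 5.3% | 56% |
| 30% | 8.0% | 76% |

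**The case against.** The strongest reply is that the definition can be read as an end state: the tube is no longer needed and no operation took place. The removal rule in Interventions fits that reading, and under it nobody has failed at baseline. The abstract and Discussion also offer decompression as an example of treatment, so not every patient need have a tube. And a journal article may condense an assessment window that the full protocol fixes.

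Much of this stands. A reader might infer that the outcome is partly decided before randomisation. The documents do not establish that: they do not say how many patients have a tube at enrolment or when need is judged. It follows only from the literal wording plus an assumed g. For the same reason the power table in Step 3 is not an estimate of the loss in this trial. The missing time point alone would be weak evidence in an article.

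What does not fall away is the conflict in the stated text, since the softer reading is not written anywhere, and the mismatch with the sizing event. Under an end-state reading the two events might come close in frequency, but that depends on a time point and a tube rule that the article does not state.

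Two further inferences should be resisted.

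- **Death as success.** One might say that a patient who dies without tube or surgery counts as a success. The Participants section drops patients who become unstable or deteriorate, so most would leave the trial first; how they are analysed is a separate question.
- **A rival outcome.** Interventions states "Therapeutic efficacy will be defined by the appearance of flatus/defecation, radiological improvement, relief of abdominal symptoms" and further signs. This sits beside tube, diet and discharge rules and reads as a bedside guide. Only section 2.6 names the primary outcome, and no figure shows how many patients would meet the list.

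**Conclusion.** The concern holds in this form: the primary outcome as worded contradicts the protocol's own description of conservative treatment, and it is not the event on which the trial was sized. Both parts rest on the text without any assumption. The sample size arithmetic is correct for surgery; the fault is that the 95% power does not belong to the defined outcome.

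The size of the effect is conditional. If the literal reading applies, a baseline share of 10% brings power to 87%, and 50% brings it to 40%, given equal shares between arms, independence from surgery and the planned surgical rates. If a softer reading was meant, the dilution may be small or absent, but the definition and its power then still have to be stated. Because this is the only primary outcome, it should be settled before unblinding.

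**What to change.** Reconcile the abstract, sections 2.4, 2.5 and 2.6 and the Discussion by amendment while the data are still blinded.

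- **Preferred.** Define primary failure as operative intervention for ASBO, the event used for sizing, from randomisation to one fixed time point. Report nasogastric tube use after randomisation as a secondary outcome.
- **If the composite is kept.** Count only tube need that arises after randomisation, say how a tube already in place is handled, fix the time point, and restate the power for that event with its own assumed rates.

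This changes what is measured, not care. Surgery and tube dates should be available from the hospital chart.

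The cost is real. Study design says recruitment began in March 2020, so this changes the primary outcome of a started trial and needs an ethics amendment and a registry update, with the reason and blinded status recorded. The event rate also falls to the surgical rate. If that lies at the 10% to 30% suggested by the Introduction, power with 41 per arm is about 29% to 76% at the planned relative risk, so the assumed 48.5% should be re-examined in the same amendment.

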## Introduction

1

Adhesive small bowel obstruction (ASBO) is one of the most common complications and is a major cause of admission after intra-abdominal surgery. The incidence of ASBO following all types of abdominal surgery is 2.4%.^[1]^ Less commonly, the adhesions may form as a result of inflammatory conditions, intraperitoneal infection or abdominal trauma.^[2]^ Definitive confirmation of ASBO is made during operative treatment. In the initial 72 hours, nonoperative management for ASBO patients is appropriate unless there are signs of peritonitis, strangulation, or bowel ischemia.^[3,4]^ Approximately 70% to 90% of patients with ASBO respond to nonoperative treatment.^[3]^ Surgery intervention for adhesions should be considered for patients with repeated ASBO or unsuccessful conservative treatment, as any delay in surgical intervention is associated with higher mortality and complication rates if nonoperative management is unsuccessful after 3 days.^[4]^ To date, the ideal management of ASBO remains disputed. Therefore, the development of a new feasible treatment to increase the likelihood of successful nonoperative treatment and reduce the recurrence of ASBO is of great clinical significance.

Laser acupuncture (LA) combines the characteristics of traditional metal-needle acupuncture and low-level laser therapy. While acupuncture has been reported to promote the recovery time of postoperative ileus in patients with colorectal cancer,^[5]^ the application of LA for ASBO is very rare, and only 1 pre-clinical study has shown low level laser therapy to be effective in preventing intra-abdominal adhesions in rabbits without compromising the strength and healing of the abdominal wall.^[6]^ We assume that conventional treatment combined with LA will be effective for reducing the need for surgery through eliminating the symptoms of ASBO. The major aim of this study is to investigate the clinical benefits and the adverse events of LA in patients with ASBO. Furthermore, we want to explore the short-term effects or changes in several serum biomarkers associated with ASBO, including serum lipase, amylase, cortisol, motilin, ghrelin, and intestinal fatty acid binding protein (I-FABP). These serum biomarkers are associated with bowel movements and injuries, as explained in the discussion section.

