### Study design

2.2

This prospective, single-center, randomized, double-blind, controlled trial began at the Department of Trauma Surgery at the Kaohsiung Chang Gung Memorial Hospital (KCGMH) in South Taiwan from March 2020 and will continue until February 2022. Ninety two participants will be randomly assigned to the experimental group (LA plus conventional treatment, n = 46) or control group (sham LA [SLA] plus conventional treatment, n = 46). All participants will receive LA or sham LA after enrollment, once daily for 6 days, during hospitalization. The study design according to Consolidated Standards of Reporting Trials (CONSORT) 2010 is depicted in Figure 1.

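### The primary outcome has no assessment day, no requirement that the obstruction has resolved, and no rule for death or dropped patients

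*Protocol article*

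**What the plan says.** Section 2.6 (Outcome measurements) gives the primary outcome as "success of conservative treatment, which is defined as no need for nasogastric tube decompression or operative intervention". It attaches no day to it. The only dated measurements there are the serum markers, "which will be checked before the intervention, on the fourth day, and on the day of discharge, respectively". Section 2.2 (Study design) sets the treatment period: "All participants will receive LA or sham LA after enrollment, once daily for 6 days, during hospitalization". It does not make the end of that period the time at which success is judged.

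Signs of recovery appear only in section 2.5 (Interventions), in a list joined by 'or' that begins: "Therapeutic efficacy will be defined by the appearance of flatus/defecation, radiological improvement, relief of abdominal symptoms". The same section allows the tube to come out once drainage is under 200 ml per day or the patient passes flatus or stool, and allows discharge once the patient tolerates solid food. None of this is tied to the primary outcome.

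Section 2.3 (Participants) drops patients who become unstable or deteriorate and does not say whether they count as successes or failures. On routine care, the Abstract states: "The initial management of patients with ASBO is nonoperative treatment such as nil per os and decompression using a nasogastric tube".

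**The concern.** Two properties of the definition cause the difficulty.

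First, need for a tube is a state that changes during the stay. Many patients will have a tube early, as part of usual care, and lose it as they improve. A definition built on that state has no fixed value until a day is named. With no day, patients with longer and shorter stays may also be observed for failure over different periods.

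Second, absence of an intervention is not the same as recovery. The trial's aim is to show that laser acupuncture helps nonoperative treatment succeed. The definition as written asks only what was not needed, not whether the obstruction resolved or the patient survived.

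At stake is the meaning of the single outcome that carries the efficacy claim. Two careful assessors could apply the published wording to the same charts and report different success rates.

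**Working it through.** **1. One patient, several readings.** Take a constructed patient who has a tube on admission. It is removed by day 4 because drainage has fallen below 200 ml per day, with no flatus or stool yet. The patient later eats solid food and goes home without an operation. Applying section 2.6:

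| Reading of the definition | Tube needed? | Operation? | Result | Resolved by then? |
|---|---|---|---|---|
| Ever during the stay | yes | no | failure | not asked |
| Day 2 | yes | no | failure | no |
| Day 4 | no | no | success | not shown |
| Discharge | no | no | success | yes, by the discharge rule |

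The result depends on the reading, and the document does not choose one. The day 4 row also shows that low drainage alone permits tube removal, so success can be scored before any sign of bowel function.

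**2. Which patients can be misclassified.**
- Still obstructed and needing a tube: failure under section 2.6. No problem.
- Still obstructed, no tube, no operation: meets the wording of success. Section 2.3 does not require a tube at entry, so such patients can exist.
- Dead, with neither tube nor operation: meets the wording literally, although section 2.3 may first drop the patient as unstable.
- Dropped for instability or deterioration: no classification given.

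**3. The planned sample size.** Section 2.4 gives surgical rates p1 = 0.129 and p2 = 0.485, α = 0.05, power 95% and dropout 10%. Sidedness is not stated; two-sided is assumed. With pooled variance and no continuity correction,

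n per arm = [1.960·√(2·p̄·(1−p̄)) + 1.645·√(p1(1−p1) + p2(1−p2))]² / (p2−p1)²

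where p̄ = (0.129 + 0.485)/2 = 0.307. The two roots are 0.652 and 0.602, and the difference is 0.356, so n = 40.6, rounded up to 41 per arm. The total is 82, and 82/0.9 = 91.1, rounded up to 92. The plan's figure is reproduced, so this point does not rest on an arithmetic error.

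**4. Illustrative cost of a stricter definition.** Assume a share m of successes is recounted as failures, equally in both arms. Each failure rate becomes 1 − (1−p)(1−m). With 41 evaluable per arm,

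power = Φ{[(difference)·√41 − 1.960·√(2·p̄·(1−p̄))] / √(sum of p(1−p))}

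| m | Failure rates | Power | Total for 95% power, after dropout |
|---|---|---|---|
| 0 | 12.9% vs 48.5% | 95.2% | 92 |
| 2.5% | 15.1% vs 49.8% | 93.4% | 100 |
| 5% | 17.3% vs 51.1% | 91.3% | 109 |
| 10% | 21.6% vs 53.6% | 86.3% | 127 |

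Example for m = 5%: (0.3382 × 6.403 − 1.960 × 0.671)/0.627 = 1.36, and Φ(1.36) = 0.913.

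The share m, and its being equal in both arms, are assumptions. The starting rates are for surgery alone and contain no tube component, so the table shows the direction and rough scale of the effect. It is not a forecast for the outcome in section 2.6.

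**The case against.** The other side has several good points.

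**The tube half of the definition does much of the work.** A reader might infer that anyone still obstructed after six days is a success. That is wrong: a patient who still needs decompression has failed. The gap is confined to patients with neither tube nor operation.

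**Death.** A reader might infer that death without surgery is scored as success. The document does not say so. Such patients may have needed a tube, or may have been dropped under section 2.3, so their status is open. The Discussion's 2.5% in-hospital mortality gives 92 × 0.025 = 2.3 deaths, but that is a background rate not limited to unoperated patients. It does not count misclassified patients.

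**The three-day statement.** The Introduction says "any delay in surgical intervention is associated with higher mortality and complication rates if nonoperative management is unsuccessful after 3 days", while section 2.5 says "If the patient presents no improvement and progresses into strangulation, peritonitis, or bowel ischemia, surgery will be recommended". A reader might see a flat contradiction. The first is background and does not define failure in this trial. Section 2.5 also allows surgery under the guidelines and the surgeons' judgement. What remains is that the handling and scoring of persistent obstruction after three days is unclear.

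**Readmission.** The Discussion reports that "recurrence or readmission due to ASBO is common, occurring in about 20% of patients", and no text counts early readmission as failure. A reader might infer that a known part of the successes is spurious. The 20% has no time window, so no such share can be derived. Whether success means this episode or a longer period is a design choice.

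**Blinding.** Participants, outcome assessors and analysts are blinded, and the surgical team does not know the allocation. Bias in favour of one arm is therefore not shown. This stands, but blinding does not supply a missing definition.

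**Condensed article.** The full protocol may name a day. However, the article states the definition itself, and as stated it cannot be applied in only one way.

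**Conclusion.** The point holds in limited form. The primary outcome is undated, does not require resolution, and leaves deaths and dropped patients unclassified. Because need for a tube varies over the stay, the success rate depends on when it is read, and a literal reading can credit a patient who is unresolved or dead with neither tube nor operation.

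The number of such patients cannot be obtained from the documents. Neither bias between the arms nor a firm contradiction over surgery is established. The power range of 91.3% to 86.3% describes a possible cost of tightening the definition, under an assumed equal recount of 5% to 10% of successes. It does not measure an existing error.

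Severity: should be fixed. It concerns the sole primary outcome, and the remedy is cheap.

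**What to change.** Amend section 2.6 as follows:

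- Assess the primary outcome for every randomised patient at one fixed time counted from randomisation.
- Define success at that time as alive, obstruction resolved by a criterion the protocol already uses (for example, its discharge criterion of tolerating solid food), and no operation for adhesive obstruction.
- State explicitly how the tube component counts at that time, including for patients who had a tube early as part of usual care.
- Count death, unresolved obstruction and drop-out for deterioration as failures.
- Report readmission and later surgery for adhesive obstruction after discharge, taken from hospital records, as a separate secondary outcome. They need not enter the primary outcome.

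Reconcile the Introduction, section 2.5 and the Discussion on persistent obstruction after three days. Which surgical rule applies is for the investigators to settle.

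Cost: an amendment and a chart check at the fixed time. The success rate will be slightly lower and some of the stated 95% power will be lost. Section 2.4 should restate power for the revised definition. On the assumptions above, keeping 95% would need about 109 to 127 patients for a 5% to 10% recount, instead of 92. Records from this hospital may miss some readmissions elsewhere.
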